### Randomization Codes

Investigators may obtain the allocation information of participants through password-protected access after the trial has concluded and the primary outcome analysis is complete. In the case of a medical emergency or serious AE, the trial manager will be asked to identify the trial arm. Following data collection, an analysis will be performed to determine if incidences of unblinding are equal in the 2 trial arms.

### Interventions

#### Attention Control Arm

Participants allocated to the attention control arm receive usual care with their GPs (ie, continued access to routine GP consultations, prescription renewals, and standard clinical management) and access to an online antidepressant fact sheet within the Beyond Blue website [51], an Australian information and support website for better mental health. This fact sheet provides educational material relevant to enrollment in the study, but participants do not receive advice regarding stopping or continuing their medication.

#### Intervention (Active) Arm

The WiserAD website has been designed through the collaboration of mental health, primary care, implementation, service user, and digital design expertise to ensure that patients who are randomized to this arm are suitably informed, eligible, supported, and prepared for antidepressant deprescribing with minimal risk.

Within 3 business days after being randomly assigned to the intervention arm, a WiserAD research nurse calls participants and guides them through the support tool. The support tool provides assessment and advice tools to develop a personalized support strategy during tapering (Multimedia Appendix 3). Participants then complete their user account setup by entering the metrics they use to monitor their own mental health, such as sleep quality, current mood, and activities. Potential reasons for fluctuations in these metrics can also be logged (Multimedia Appendix 3) and flagged by participants when these indicate a drop in mood relative to that identified at the start of the intervention. Participants complete the tapering schedule and user account independently and/or with the WiserAD research nurse. The WiserAD research nurse follows up with participants at routine and mutually agreed times (eg, 1-week, 2-week, or monthly intervals) for a period of no more than 6 months.

GPs are informed about patients allocated to the intervention arm of the study via an email from the research team. Participants are encouraged to discuss any planned medication changes with their GPs, seek clinical advice if they have concerns, and receive corresponding prescriptions according to the tapering plan. Participants may continue in the study without explicit permission from their GPs. Their GPs can modify the tapering schedule if they feel that it is not appropriate and/or if the WiserAD research nurse informs them that their patients are not responding well to the reduced dosage, as indicated by the daily tracker. A practitioner-facing interface in the WiserAD website allows the study team and the GPs to oversee the progress of patients.

The daily symptom tracker is monitored by the WiserAD research nurse or trial manager to closely monitor the mood and response of patients to the tapering schedule.

A standard operating procedure (SOP) is followed for patients who do not complete the daily tracker, show a major decline in current mood, or show symptoms that have been identified as warning signs for a declining mood state in their daily tracker (see the Risk Management section). As part of the SOP, the PHQ-9 [53] is completed to assess the severity of depressive symptoms.

Participants continue to have access to the WiserAD website until trial completion (after all trial participants complete the final follow-up survey). They also receive a link to access the antidepressant factsheet within the Beyond Blue website.

### Outcomes

#### Overview

Outcome measures are assessed at 3, 6, 12, and 18 months after randomization to allow for shorter- and longer-term monitoring and to inform implementation and prescribing guidelines (Table 1). All measures are collected via a REDCap link sent to participants; however, they may also complete these assessments over the phone with a researcher.

#### Primary Outcome

The primary outcome is the difference in the proportion of eligible individuals successfully ceasing antidepressant use at 6 months between the intervention and attention control arms. Successful cessation is defined as no antidepressant use and the absence of clinically significant depressive symptoms. Antidepressant use is assessed via self-report (ceased/not ceased) and validated where possible using PBS data. Depressive symptom severity is assessed using the PHQ-9, and the absence of clinically significant symptoms is defined as a PHQ-9 score of <10. The PHQ-9 provides a conservative estimate of depressive symptom severity, and thus, patients are less likely to be misclassified as having an absence of clinically significant depressive symptoms when they report depressive symptoms with a PHQ-9 score of >10, which indicates moderate/severe depressive symptoms. The PHQ-9 is commonly used in general practice trials.

#### Secondary Outcomes

Secondary outcomes are assessed to capture any changes in antidepressant use and longer-term management, mood, and activities. These include differences between the intervention and attention control arms in (1) the proportion of patients maintaining a reduced antidepressant dosage at 6 months after randomization; (2) the proportion of patients successfully ceasing antidepressant use at 3, 12, and 18 months; (3) mean anxiety symptoms at 3, 6, 12, and 18 months measured using the Generalized Anxiety Disorder-7 (GAD-7) [56]; and (4) mean patient engagement and motivation at 3 and 6 months measured using the Patient Activation Measure (PAM) [58,63].

### Economic Evaluation

A comprehensive economic evaluation of quality of life and health care use (medical and pharmaceutical) will be conducted using a study-specific self-report Resource Use Questionnaire-4 (RUQ4) adapted from a questionnaire used in a previous trial conducted by our group [64,65]. The RUQ4 will record the type, frequency, and duration of health service use by participants through direct and indirect cost savings in the preceding 3 months and will be collected at 3, 6, 12, and 18 months. Through the assessment of measures of social activities, such as work and benefits, the impact of mental health can be assessed. The RUQ4 will be integrated into the website and will follow a conditional logic model, where subsequent questions will only be presented if a participant’s previous response requires further information. This approach is intended to help with the completion of the questionnaire by reducing the burden on participants.

The Assessment of Quality of Life-4D (AQoL-4D), a validated measure, will be used to assess the impact of mental and physical health on everyday quality of life [59]. For participants who provide additional consent, reliable health service use data will be obtained from the MBS and PBS. These records provide supporting data and information regarding primary and secondary care visits and prescription medications through Australia’s universal health care system.

The actual cost of the intervention will be determined and captured using financial and provider records.

Mediators will be measured at baseline and 3, 6, 12, and 18 months. To understand possible mediators, the following will be recorded: (1) participant beliefs and motivations related to their relationships with medications, which will be measured using the Beliefs about Medicines Questionnaire (BMQ) [57]; (2) accountability and engagement, which will be measured using the Accountability Measurement Tool (AMT) [61] and User Engagement Scale-Short Form (UES-SF) [62], respectively; and (3) signs and symptoms typically associated with reducing antidepressants, which will be assessed (text responses) during contact with the WiserAD research nurse.

Other measures include data from the daily tracker, retention, and compliance with the tapering schedule (assessed using analytic data collected on the WiserAD website).

### Process Evaluation (Realist Approach)

The intervention has been evaluated with a realist approach [66,67] to explore the experiences of 13 participants, using qualitative interviews (conducted over the phone or via Zoom videoconference software) and quantitative data from the baseline and 3-month follow-up surveys [40]. The interviews followed a narrative approach to elicit rich responses with minimal prompting [68] and focused on participant engagement with the study and study website and the expectations for online tapering support. The evaluation followed the Pawson and Tilley realist approach [66] and RAMESES II (Realist and Meta-Narrative Evidence Syntheses: Evolving Standards) guidance, where the analysis used an abductive realist logic to generate and refine context-mechanism-outcome configurations, with mechanisms conceptualized as interactions between program resources and participant reasoning [69]. Full methodological details, including the interview guide and analytic procedure, are provided in a published realist-evaluation protocol and related outcomes paper [40,50].

### Sample Size

We require 340 patients at baseline (170 patients per arm) for 80% power with a 5% significance level (2-sided test) to detect a 20% difference in the proportion of patients who successfully cease antidepressant use at 6 months between the intervention and attention control arms (36% vs 16%), after allowing for up to 50% attrition at 6 months (primary outcome). The sample size is based on the proportion of participants who cease antidepressant use at 6 months and for whom the PHQ-9 score is <10 (primary outcome).

The initial target sample size was 312 patients at baseline (156 patients per arm) for 90% power (5% significance level and allowing 30% attrition over 18 months). As of June 25, 2025, the 6-month survey response rate was closer to 50%, which was lower than anticipated. Thus, with approval from the Data Monitoring Committee’s independent statistician, the final target sample size was increased from 312 to 340 while maintaining at least 80% power for the primary outcome.

In a 10-year longitudinal study of general practice attendees, the estimated natural rate of cessation among patients with PHQ-9 scores below the threshold was between 10% and 16% annually [64,65,70]. Given that willingness to review medication is an inclusion criterion for this study, we expect the cessation rate in the attention control arm to be at the high end of this range (16%). Published primary care deprescribing interventions show no improvement over this natural cessation [71]; thus, we have determined our minimally important effect size of 20% based on studies of more intensive (albeit nonprimary care) deprescribing interventions, which have achieved 36% antidepressant cessation [72]. To achieve the target sample size, we need to invite 940 eligible patients. This value is based on a previous deprescribing RCT [27], which demonstrated that approximately one-third of eligible patients consented to a deprescribing trial.

### Data Collection and Management

All data of eligible trial participants will be collected through the study website, WiserAD [73], and the embedded University of Melbourne REDCap system [55], including consent forms and health economics questionnaires.

The WiserAD website is a secure, password-protected online platform that uses encrypted HTTPS connections to ensure data privacy and integrity. REDCap is a secure, web-based platform designed to support data capture for research studies, providing (1) an intuitive interface for validated data entry; (2) audit trails to track data manipulation and export procedures; (3) automated export functions to common statistical packages; and (4) tools for integration and interoperability with external data sources.

Trained research assistants will enter data using individual, password-protected accounts, and participants will receive a unique login and password to access the study website and IST, followed by secure, personalized links to complete follow-up study measures in REDCap. Each participant will be assigned a unique ID to link all data throughout the study while protecting confidentiality. Participants will receive follow-up reminders at scheduled time points, as described in the Retention section.

All study raw data will be downloaded from secure Australian-based servers and stored on password-protected servers at the University of Melbourne, with access restricted to authorized study team members. Data transfers will occur via encrypted HTTPS connections, and daily automated backups will be securely stored. Data exported from WiserAD and REDCap for analysis may initially contain identifying information, such as contact details; however, these identifiers will be removed during data cleaning to produce deidentified datasets for all analyses.

Data cleaning and processing will be performed using Stata (version 17). Datasets from different collection points will be merged to form the final analysis dataset. Data will be scored and processed according to the respective questionnaire manuals and scoring guidelines to ensure accuracy, consistency, and validity. Data quality will be maintained through built-in validation rules and periodic quality assurance checks by the data manager, with all access events and changes automatically logged.

Deidentified datasets will be retained for a minimum of 5 years following publication of study results, after which they will be securely archived or destroyed in accordance with the University’s research data management policy.

### Retention

The following steps are taken to limit missing responses for the primary outcome and minimize participant attrition:

Reminder emails or text messages are sent to all participants 72 and 24 hours prior to their follow-up due date. If they do not complete the follow-up, another text or email is sent once a week for 2 weeks. If they still fail to respond, a researcher calls them via telephone up to a maximum of 4 times over the next 2 weeks. Participants also have the option to complete the follow-up measures over the phone with a researcher. Participants are declared nonresponders for the follow-up time point if they do not respond within 1 month of the time point. Only participants who actively inform us that they wish to withdraw are marked as withdrawn in the study log; otherwise, they are assumed to be lost to follow-up at each time point.Participants in the intervention arm who are not responding to their daily symptom trackers are contacted according to the SOP for risk management. If it becomes clear that they are well but not willing to complete the tracker, the WiserAD research nurse discusses how to proceed, initially suggesting to complete the tracker every other day.Participants who do not consent to the collection of their health economics information are reminded of this option at each follow-up time point.Participants who complete their routine follow-up questionnaires (at least the primary measure) are eligible to participate in a monthly prize draw to win a shopping voucher worth AUD $100 (approximately US $71).

People who wish to take part in the study but are not eligible may be asked to consent to take part in short, anonymous surveys about their current use of antidepressants and their understanding of antidepressants, and may be offered a chance to discuss these with a researcher in a series of qualitative interviews designed to gauge participants’ thoughts and feelings about their medications and why they consider stopping. These participants are not included in the main trial analysis but may provide valuable qualitative evidence for the deprescribing literature.

### Statistical Methods for the Primary and Secondary Objectives

Descriptive statistics will be used to review the demographic characteristics of the participants and assess the balance of participants within the 2 trial arms. We will use generalized linear models with identity and logit link functions and binomial distributions for both models to estimate the between-arm difference in the proportion of participants ceasing antidepressant use and having a PHQ score of <10 (absolute measure) and to assess the odds ratio (relative measure) at each time point (3, 6, 12, and 18 months), respectively. Both models will use generalized estimating equations with robust SEs (accounting for repeated outcome measures on individuals) and include stratification factors (general practice/state) and time as covariates. Multiple imputation may be used to handle missing data, and this is contingent upon an examination of the patterns of the missing data in a blinded review of the data. A similar approach will be undertaken for secondary binary outcomes. For secondary continuous outcomes, a constrained longitudinal data analysis will be used, with response variables consisting of all outcomes measured at each time point (0, 3, 6, 12, and 18 months). Linear mixed-effects models using restricted maximum likelihood, with random intercepts for individuals, will be used to estimate the difference in means between the trial arms at each measurement time point. Regression analyses will adjust for baseline outcome measures (when appropriate), the stratification variable (site/state), time, and the trial arm (intervention/attention control). A 2-way interaction between arm and time will be included, with the exception of the baseline, where means are constrained to equality. The estimated intervention effect will be reported as between-arm differences in proportions and odds ratios for binary outcomes and between-arm differences in means for continuous outcomes at each time point (3, 6, 12, and 18 months), with their respective 95% CIs and *P* values. There will be no adjustments for handling the multiplicity of testing, and no formal interim analysis is planned.

Primary analyses will use an intention-to-treat strategy, where all individuals will be analyzed in the trial arm to which they have been randomly allocated [74]. Additional sensitivity analyses will include adjustment of prespecified prognostic baseline variables (eg, age and duration of antidepressant use) in the regression models, using complete cases only and using pattern-mixture models, to assess the robustness of the missing data assumption. A detailed statistical analysis plan will be developed to outline supplementary analyses, such as methods for handling missing data and assessing the impact of nonadherence on the estimated intervention effect, and subgroup and exploratory analyses. The statistical analysis plan will be made available prior to the commencement of any statistical analysis. Analyses will be conducted in Stata 17.0 or later.

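### The random-intercept model for continuous secondary outcomes fixes one variance and one correlation for five unequally spaced visits, so visit-specific standard errors can be wrong, chiefly for late GAD-7

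*Protocol article*

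**What the plan says.** All points are in the protocol article. Unless noted, they come from Statistical Methods for the Primary and Secondary Objectives.

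- The continuous outcomes are analysed jointly, "with response variables consisting of all outcomes measured at each time point (0, 3, 6, 12, and 18 months").
- The mean model is flexible: "A 2-way interaction between arm and time will be included, with the exception of the baseline, where means are constrained to equality".
- The model class is "Linear mixed-effects models using restricted maximum likelihood, with random intercepts for individuals". No random slope, residual covariance structure or robust variance is named for it.
- Robust standard errors appear one step earlier, for the binary outcomes: "Both models will use generalized estimating equations with robust SEs (accounting for repeated outcome measures on individuals").
- The reported results are "between-arm differences in means for continuous outcomes at each time point (3, 6, 12, and 18 months), with their respective 95% CIs" and P values, without multiplicity adjustment.
- Secondary Outcomes lists "mean anxiety symptoms at 3, 6, 12, and 18 months measured using the Generalized Anxiety Disorder-7 (GAD-7"). The Patient Activation Measure (PAM) is a secondary outcome at 3 and 6 months only.
- Sample Size reports that "the 6-month survey response rate was closer to 50" per cent, so a large share of follow-up values will be missing.

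**The concern.** A random intercept with independent residuals implies compound symmetry: visits 3 months apart and visits 18 months apart are assumed equally correlated, and every visit is assumed to have the same variance. With complete data the model must then report the same standard error at month 3 as at month 18, whatever the data show. Because baseline is part of the response, the assumed covariance also decides how far each visit is adjusted for baseline and, with heavy dropout, how missing values are implicitly filled in.

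The late GAD-7 results are at stake. Anxiety not worsening through 18 months is a stated secondary objective, and each visit gets its own interval and P value. Correlation between symptom scores commonly falls as the gap widens. Spread may also grow after entry, since participants enter with low depressive scores.

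**Working it through.** **The plan's own figures.** The article gives no figure for the continuous outcomes. Its sample size, for the binary primary outcome, reproduces: 36% v 16%, 80% power and continuity correction give 85 per arm; 85 / 0.5 = 170 per arm, 340 in total. I use 170 per arm below.

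**Assumed inputs.** SDs, correlations, and retention other than 50% at 6 months. Dropout is taken as monotone and unrelated to outcome.

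**Complete data.** Let *s*² and *r* be the single variance and correlation that the random-intercept model settles on, and σ₀, σₜ, ρₜ the true SDs and the true correlation of visit *t* with baseline. The estimated effect is the arm difference at *t* minus *r* times the arm difference at baseline.

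- Reported SE² = (2/n) · *s*²(1 − *r*²)
- True SE² = (2/n) · (σₜ² − 2*r*ρₜσ₀σₜ + *r*²σ₀²)
- Type I error = 2[1 − Φ(1.96 × reported SE / true SE)]

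*Equal SDs, correlation falling linearly from 0.70 (3-month lag) to 0.40 (18-month lag).* The ten visit pairs have lags 3 (twice), 6 (three times), 9, 12 (twice), 15 and 18 months. So *r* = (2×0.70 + 3×0.64 + 0.58 + 2×0.52 + 0.46 + 0.40)/10 = 0.58, and 1 − *r*² = 0.6636.

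- Month 3: 1 − 2(0.58)(0.70) + 0.3364 = 0.5244. Ratio √(0.6636/0.5244) = 1.125, type I error 2.7% (interval too wide).
- Month 18: 1 − 2(0.58)(0.40) + 0.3364 = 0.8724. Ratio √(0.6636/0.8724) = 0.872, type I error 8.7% (too narrow).

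*Same correlations, SDs 3, 4, 4.5, 4.8, 5.* *s*² = 93.29/5 = 18.66. The mean covariance is 10.43, so *r* = 0.559 and *s*²(1 − *r*²) = 12.82. At month 18: 25 − 2(0.559)(0.40×3×5) + 0.3128×9 = 21.1. Ratio 0.779, type I error 12.7%.

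**With dropout** (60/50/45/40% retained at 3/6/12/18 months), type I error in %, nominal 5:

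| Assumed truth | 3 mo | 6 mo | 12 mo | 18 mo |
|---|---|---|---|---|
| Compound symmetry, correlation 0.6 | 5.0 | 5.0 | 5.0 | 5.0 |
| Equal SD, correlation 0.7 to 0.4 | 2.9 | 4.0 | 6.6 | 9.6 |
| Equal SD, correlation 0.8 per 3 months | 1.2 | 3.5 | 8.5 | 12.1 |
| Correlation 0.7 to 0.4, SD 3.5 to 4.5 | 3.2 | 5.1 | 8.9 | 12.4 |
| Correlation 0.7 to 0.4, SD 3 to 5 | 3.4 | 7.1 | 11.4 | 15.1 |
| Correlation 0.6 throughout, SD 3.5, 5, 4.5, 4, 3.8 | 11.1 | 7.2 | 4.1 | 3.1 |

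**Second retention pattern** (62/50/43/38%):

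- Equal SDs: 7.5% at 18 months for correlation 0.66 to 0.51, and 9.8% for 0.7 to 0.4.
- SD also rising to 4.5: about 11 to 14%. At the upper end (SD from 3, correlation 0.67 to 0.38) the reported SE is 0.54 against a true 0.71, a ratio of 0.76.
- SD peaking early: about 11% at 3 months and 3% at 18.

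**Cost of the alternative.** Under true compound symmetry the unstructured model has the same large-sample SEs. In every other row of the table its SE is no larger than the true SE of the random-intercept estimate.

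**The case against.** - **The direction is not fixed by the documents.** A reader might infer that the late intervals will be too narrow. The article gives no SDs or correlations. There is no error under compound symmetry, and the late intervals are conservative if the spread peaks early. This stands, and the point is conditional for that reason.
- **PAM.** A reader might extend the late-visit problem to patient activation. It is collected at every visit but is a secondary outcome only at 3 and 6 months, so the late-visit concern applies to GAD-7 at 12 and 18 months. At 3 months the decay cases give intervals that are too wide. This stands.
- **Eligibility screening.** The cut-off is on PHQ-9, not on GAD-7 or PAM, so any narrowing of baseline anxiety is indirect and of unknown size. This stands. Correlation decay alone, with constant SD, still gives 7.5 to 9.8% at 18 months.
- **The analysis plan may say more.** The article defers a detailed plan, and residual structure, degrees of freedom and convergence rules are ordinary content for it. This stands in part: it cannot be claimed that no protection exists anywhere. But the article does choose a covariance for the main model, and what it defers is supplementary work such as missing data, nonadherence and subgroups. A plan that follows the article would carry the restriction forward.
- **Missing data.** Complete-case and pattern-mixture sensitivity analyses are planned. They test the missing-data assumption and do not correct the standard errors of the main model.

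**Conclusion.** The point holds in conditional form. The stated covariance is more restrictive than five visits over 18 months warrant, and no stated safeguard covers the continuous outcomes.

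- **Size at 18 months, GAD-7:** about 7 to 10% type I error with moderate correlation decay and constant SD, and about 11 to 14% if the SD also grows. Steeper assumptions in the table reach 12% and 15%.
- **Size at 12 months, GAD-7:** the same decay cases give about 6 to 11%.
- **Other directions:** under decay the 3-month interval is too wide, and an early peak in SD moves the excess error to the early visits.

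The sizes rest on assumed SDs, correlations and retention; only the 50% at 6 months comes from the article. The primary outcome, analysed by GEE with robust standard errors, and the sample size are not touched. This is worth changing before the analysis plan is final, but it does not threaten the trial's main conclusion.

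**What to change.** Keep the constrained longitudinal mean model and REML. Replace the random-intercept covariance with an unstructured residual covariance across the five visits, with Kenward-Roger or Satterthwaite degrees of freedom. Name a fallback for non-convergence in advance, such as a heterogeneous Toeplitz structure, or the random intercept with cluster-robust standard errors. The robust fallback corrects the standard errors but still relies on the restrictive covariance for implicit imputation, so it should come last. Check beforehand that the software offers it together with REML.

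The cost is one sentence in the analysis plan and a model option. The unstructured form has 5×6/2 = 15 covariance parameters instead of 2, and carries some risk of non-convergence. With 340 baselines and, at an assumed 38% retention, about 0.38 × 340 = 129 responses at 18 months, this should be manageable. Precision lost if compound symmetry holds is essentially nil. No new data are needed.
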